#### Control group

2.5.2

GPs in the control group will receive no specific training or intervention. They will provide usual care, which includes unrestricted access to physiotherapy, imaging, medication, sick leave, and specialist referral (including interdisciplinary rehabilitation) as clinically indicated. This reflects real-world Swiss primary care practice and is considered the best choice comparator. A 30-min information session on recruitment procedures is provided to ensure comparable enrolment processes without contaminating usual care. After all follow-up data has been collected from participants recruited within a control arm quality circle, that quality circle will be offered the same training as received by those in the intervention group.

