### Trial context and design

2.1

This study employs an effectiveness-implementation hybrid type 1 design, in which clinical effectiveness is the primary focus while implementation processes are evaluated as secondary objectives [[25], [26], [27]]. Effectiveness will be evaluated through a pragmatic, cluster-randomized controlled superiority trial comparing PRIME with usual care at system, practitioner and patient levels. The 20 quality circles (clusters) will be randomly allocated to the intervention or control group at a 1:1 ratio (10 intervention clusters, 10 control clusters). All clusters are drawn from a single healthcare network (“Réseau Delta”) in French-speaking Switzerland. Within this network, GPs take part in regular quality circles—small groups of about five to ten physicians—that offer a structured setting for peer exchange and continuous practice improvement. Implementation processes will be investigated using quantitative and qualitative methods [25,26].

This study was approved by the Regional Ethic Committee (CER-VD, 2025-01380). Healthcare practitioners participating in the study and all patients signed an informed consent. The study is registered on clinicaltrials.gov (NCT07137065). Patient recruitment is planned from February 2026 to June 2027.

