#### Healthcare professionals

2.4.1

Quality circles will be recruited from the Réseau Delta in French-speaking Switzerland (Fig. 1). Eligible quality circles will be identified and contacted through the network coordination team. Quality circles in which at least three GPs agree to participate will be included prior to randomization, ensuring that GPs and the research team remain blinded to group allocation during recruitment. Small quality circles (≤4 GPs) will be merged with another geographically proximate quality circle before randomization to form a single cluster. Additional GPs may be added to randomized clusters if they provide consent after randomization. GPs will provide written informed consent at the start of the pre-study session.

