Adverse events (AEs) will be monitored through both passive and active surveillance. Passive surveillance involves continuous self-reporting by participants to the research team or their treating GP. Active surveillance is conducted through REDCap, where participants are prompted to report health events; any declaration triggers an automated alert to the research team for evaluation. Serious AEs are defined as events resulting in death, hospitalization or in persistent disability and are not anticipated given the non-invasive, non-pharmacological nature of the intervention. The expected non-serious AE is a fluctuation or increase in back or leg pain symptoms; this type of event is sometimes referred to as a normal reaction and will not be reported by GPs or physiotherapists.

Healthcare professionals baseline data will include general characteristics such as age, gender, years of clinical experience, practice setting and type, and prior training in LBP management. Patient baseline data will include demographics and social determinants of health. Participants will receive online questionnaire links by SMS and email. To limit participant burden, baseline data will be collected over two timepoints: on the day of the initial GP consultation and two days later. Follow-up assessments will occur at 10 days, 6 weeks, and 3, 6, 9, and 12 months (Supplementary Material S4). To promote retention, non-respondents will receive up to three reminders, followed by telephone contact if needed. Participants may receive financial compensation of up to CHF 50 based on questionnaire completion.

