### Sample size

2.8

The sample size was calculated based on the primary patient-level outcome (RMDQ) and the primary practitioner-level outcome (imaging prescription rate) [61]. Assuming 10 clusters per group with a mean of 20 patients per cluster, the study has 80.97% power to detect a between-group difference of 2.5 points on the RMDQ (SD = 6.0), using an intracluster correlation coefficient (ICC) of 0.05 and a two-sided significance level of 0.05 [62]. The ICC of 0.05 and the 20% allowance for loss to follow-up were informed by Darlow et al. (2019), who used the same assumptions in a comparable cluster-randomized primary care study evaluating the RMDQ. For back-related imaging, the same cluster structure provides 81.99% power to detect a 15% absolute reduction from a baseline imaging rate of 30%, assuming an ICC of 0.01 [35,63]. Allowing for a 20% dropout rate, a total of 500 patients will be recruited (25 patients per cluster).

Variation in cluster size was assessed using the coefficient of variation approach [64]. Given a minimum of 15 and a maximum of 35 patients per cluster (mean = 25), the coefficient was < 0.23 and considered negligible. Therefore, no adjustment was applied, and recruitment will stop once a cluster reaches 35 patients. No formal sample-size calculation was performed for cost-effectiveness due to limited Swiss data. We aim to recruit at least 100 general practitioners (approximately five patients per GP) and a minimum of 30 physiotherapists.

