For patient-level primary outcome, an exploratory non-inferiority analysis will be performed using a margin of −2.5 points on the RMDQ, reflecting the possibility that the intervention may be acceptable if non-inferior and cost-saving. Pre-planned mediation analyses will examine the role of psychological factors in patient outcomes [70]. Different secondary analyses will be conducted, including the number of participants in each group that reach 30%, 50% and 70% of improvement on the RMDQ, as well as the number of participants reaching the patient acceptable symptom state (≤4 on RMDQ) [71]. All analyses will be performed using SAS (version 9.4) and Stata or R. Deviations from the statistical analysis plan will be documented and reported.

Given the three primary outcomes operating at distinct and complementary levels (system, practitioner, patient), findings will be interpreted jointly but are considered complementary rather than causally dependent. Each outcome is analyzed and reported independently, without formal alpha correction across levels. Discordant findings across levels are anticipated and theoretically meaningful: the three outcomes cover different domains serving different decision-making purposes, consistent with the GRADE Evidence to Decision framework [72].

Participants who withdraw or fail to complete baseline questionnaires will be considered screening failures and excluded from the trial. To ensure sufficient power at the primary endpoint, recruitment will continue until at least 200 patients per group have completed the 6-month assessment; consequently, total recruitment may exceed 500 participants. GP dropouts during the study period will not result in patient exclusion. Patient outcomes will be analyzed according to the cluster allocation at enrolment *(intention-to-treat principle)*.

For cost-effectiveness analyses, missing cost data will not be imputed; instead, they will be complemented where available with health insurance records. In case of discordance between data sources, patient questionnaire data will be considered primary and insurance data will be used for validation and to complement missing values. For outcomes other than costs, multiple imputation assuming data Missing at Random will be performed using SAS PROC MI for variables with more than 10% missing data, incorporating covariates, intervention group, and cluster information.

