Several risks and limitations should be considered. First, patient recruitment is led by GPs, which may introduce selection bias despite mitigation strategies. Second, recruitment may also be challenging given GP workload, even though we included a high number of GPs in the study and developed recruitment strategies with a low time burden. If recruitment targets are not achieved, the recruitment period may be extended and additional eligible clusters may be recruited. If the final sample size remains below target, this will result in greater imprecision of the effect estimates and an increased risk of type II error, which will be acknowledged in the limitations. Third, the geographically limited setting increases the risk of contamination, particularly if patients in the control group consult trained physiotherapists. This will be monitored through patient questionnaires that will capture whether control-arm participants consulted a PRIME-trained physiotherapist. In such cases, sensitivity analyses will be conducted to assess the impact on primary outcomes. GP-level contamination is minimized by excluding GPs from the same practice who belong to different quality circles, and by restricting intervention materials (training content, digital tools, reminder emails) to intervention clusters only. The risk that control GPs will be passively exposed to intervention components in a meaningful way is low, and the risk that any exposure leads to important practice change to be even less [19]. Fourth, baseline data were collected after the initial GP consultation, which may limit evaluation of early consultation effects. Fifth, although LBP prevalence in primary care is not known to vary substantially by season, temporal factors such as GP availability during holiday periods or staggered training schedules could influence recruitment rates. Cluster-level recruitment monitoring will be conducted throughout the enrolment period. Finally, the effectiveness of complex behavioral interventions depends on fidelity and engagement, which may vary across clinicians, and co-interventions cannot be fully controlled. Accordingly, this trial primarily evaluates the effectiveness of interventions targeting healthcare professionals rather than individual clinical encounters.

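### Control quality circles are offered PRIME training one at a time, before follow-up in the whole control arm is complete; this conflicts with the stated contamination safeguard and mainly exposes the 12-month outcomes, probably slightly

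*Protocol article*

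**What the plan says.** - **Trigger for training control circles** (section 2.5.2, Control group): the offer is tied to the end of follow-up in a single circle: "data has been collected from participants recruited within a control arm quality circle, that quality circle will be offered the same training". The condition refers to the circle's own participants only.
- **Contamination safeguard** (section 3, Discussion): GP-level contamination is limited by two measures. One is the rule on shared practices. The other is "restricting intervention materials (training content, digital tools, reminder emails) to intervention clusters only". The planned monitoring and sensitivity analysis concern control patients who see a PRIME-trained physiotherapist. Control GPs trained under section 2.5.2 are not mentioned.
- **Calendar** (sections 2.1 and 2.6): "Patient recruitment is planned from February 2026 to June 2027". "Follow-up assessments will occur at 10 days, 6 weeks, and 3, 6, 9, and 12 months".
- **When enrolment ends**: section 2.8 says "recruitment will stop once a cluster reaches 35 patients". Section 2.12 says "recruitment will continue until at least 200 patients per group have completed the 6-month assessment". The Discussion also allows a longer recruitment period and additional clusters.
- **Unit** (section 2.4.1): "Small quality circles (≤4 GPs) will be merged with another geographically proximate quality circle before randomization to form a single cluster". Randomization is by cluster, whereas the training offer is worded by circle.

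**The concern.** Delayed training of the control arm normally waits until the comparison is over. Here it waits only until one circle's part is over. Because circles stop enrolling at different times, some control GPs will know the PRIME content while patients of other control circles, in the same healthcare network, are still being followed. If that content spreads, control care moves towards PRIME and the contrast between arms shrinks. The outcome most at stake is the system-level primary, since costs and QALYs accrue over 12 months; 12-month imaging, a secondary outcome, is exposed in the same way.

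The two sections also cannot both stand as written. One gives control circles the training while the trial may still be running; the other relies on that training content being confined to intervention clusters.

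**Working it through.** **Inputs.** Recruitment from February 2026 to June 2027 is 17 months (month 0 = start of February 2026). Follow-up is 12 months. There are 10 clusters per arm, 25 patients recruited per cluster on average, and a cap of 35. The last 6-month assessment is then due at month 17 + 6 = 23 and the last 12-month assessment at month 17 + 12 = 29. Mean accrual per cluster is 25/17 = 1.5 patients a month. The plan states no figure for the stagger itself, so there is none to reproduce.

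**Step 1: calendar arithmetic.** Let a circle's last enrolment be in month T. It can be trained from month T + 12. Its release then overlaps:
- enrolment elsewhere by 17 − (T + 12) = 5 − T months;
- the 6-month window of the last patients by 23 − (T + 12) = 11 − T months;
- the 12-month window of the last patients by 29 − (T + 12) = 17 − T months.

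If another circle enrols uniformly over 17 months, the share of its patients still inside 12 months at release is (17 − T)/17, and inside 6 months (11 − T)/17, with negative values set to zero.

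| T | Rate needed to reach 35 by T | Overlap with enrolment | Share inside 6 months | Share inside 12 months |
|---|---|---|---|---|
| 5 | 7.0 per month | 0 | 35% | 71% |
| 8 | 4.4 | 0 | 18% | 53% |
| 10 | 3.5 | 0 | 6% | 41% |
| 12 | 2.9 | 0 | 0% | 29% |
| 15 | 2.3 | 0 | 0% | 12% |

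Overlap with enrolment needs a circle to fill before month 5, at more than 7 patients a month against a planned 1.5, so the planned dates practically exclude it. Overlap with the 6-month window needs T below 11, that is at least 35/11 = 3.2 a month. Overlap with the 12-month window occurs for any T below 17.

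**Step 2: how large is T likely to be?** The protocol does not say, so this rests on an assumed model: cluster accrual rates gamma-distributed with mean 25/17 per month and coefficient of variation (CV) 0.23, 0.4 or 0.5; Poisson arrivals; cap 35; release 12 months after the circle's last enrolment; 4,000 simulated trials per setting. Figures are medians.

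| | Recruitment stops at month 17 | Recruitment follows the 200-completers rule, 20% loss |
|---|---|---|
| Recruitment stops (month) | 17 | 24.4 / 26.1 / 27.7 |
| First control release (month) | 26.4 / 24.8 / 23.7 | 27.6 / 25.4 / 24.2 |
| Gap to last release (months) | 2.5 / 4.1 / 5.2 | 8.3 / 12.4 / 15.0 |
| Other control patients inside 12 months | 15 / 23 / 28% | 29 / 39 / 45% |
| Other control patients inside 6 months | about 0% | 6 / 15 / 21% |

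The middle column agrees with Step 1. First releases at 26.4, 24.8 and 23.7 mean T = 14.4, 12.8 and 11.7, and (17 − T)/17 gives 15%, 25% and 31%. The simulated shares are slightly lower because capped circles contribute no late patients. The stagger comes from circles that hit the cap and also from circles whose last patient happened to enrol early: at 17/25 = 0.7 months between patients on average, last enrolments do not coincide.

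**Step 3: the 200-completers rule.** With 20% loss, 200 completers need 200/0.8 = 250 enrolled per arm. If 250 are reached at month 17, the 200th completer arrives at about month 17 + 6 = 23. Read literally, the rule therefore keeps recruitment open past June 2027 even at planned accrual. Under it, the median first release precedes the close of recruitment at CV 0.4 and 0.5, but not at CV 0.23 (27.6 against 24.4).

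**The case against.** **What a reader might infer.** The text could be read as placing PRIME-trained GPs in charge of control patients, or as training control circles while others still enrol. The documents do not support either for the planned schedule. A circle is trained only after its own participants have finished, so its GPs have no trial patient left in follow-up. Overlap with enrolment is practically excluded on the stated dates (Step 1). Both points stand.

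**Spill-over is the only route, and it is limited.** Section 2.3.1 keeps GPs of one practice from taking part through two circles. The Discussion judges passive exposure of control GPs unlikely and resulting practice change less likely still. Ten trained intervention circles sit in the same network throughout, so a few late control circles add to a risk already accepted. In addition, PRIME's GP components act at the first consultations, 10 days and 6 weeks, which patients beyond 6 months have passed. These points stand and keep the likely effect small. They do not remove the conflict between sections 2.5.2 and 3.

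**The simulated variation is generous.** Section 2.8 expects a CV of cluster size below 0.23. The assumed accrual CVs of 0.23, 0.4 and 0.5 give cluster-size CVs at month 17 of about 0.27, 0.36 and 0.42. The planned variation therefore points to the low end of the range or somewhat below it. The larger figures need recruitment to run to months 24–27 with about 590–630 patients, which section 2.12 permits but which is not the planned case of 500 by June 2027.

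**Merged clusters.** Training one half of a merged cluster before the other is an inference from the wording. Section 2.1 equates circles with clusters, and section 2.5.1 delivers GP training at cluster level. The wording still allows it.

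**The conflict is partial.** Section 2.5.2 offers the training, not the reminder emails or digital tools. Of the three items the Discussion lists, only training content clearly conflicts.

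**Conclusion.** The point holds in a limited form. Training is released per control circle, nothing ties it to completion of the control arm, and this is inconsistent with the Discussion's safeguard and its monitoring plan.

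On the planned dates the first control circle could be trained about 2.5 to 5 months before the last, with 15–28% of other control patients still inside 12 months and almost none inside 6 months. Those shares count patients still in follow-up, not patients exposed. The share actually contaminated is unknown and probably small, and no bias in any estimate has been shown. The exposure is mainly to months 6–12 of the cost and QALY primary and to 12-month imaging.

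The 6-month disability and imaging primaries, and enrolment itself, come into play only if recruitment runs on under section 2.12 or is extended as the Discussion allows. In that case there is a further gap: nothing bars a trained control circle with fewer than 35 patients from enrolling again.

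The sizes rest on the assumed accrual model; the textual conflict does not. This is a cheap improvement rather than a serious design flaw, and no sample-size figure changes.

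**What to change.** Change section 2.5.2 so that training is offered to control circles only after recruitment has closed trial-wide and the 12-month data of the last control-arm patient have been collected.

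If that delay is unacceptable, the minimum is to release by randomized cluster rather than by single circle, and to close a trained cluster to further enrolment. This leaves some overlap with other clusters' 12-month follow-up.

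In either case, log each release date and reconcile the Discussion's statement on restricted materials with section 2.5.2.

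The cost is a sentence or two of protocol text and a longer wait for control circles that finish early: a few months on the planned schedule, and about 8 to 15 months under the assumed accrual model if recruitment follows the 200-completers rule.

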#### Concomitant care

2.5.3

Participants in both groups may receive any additional care (concomitant care) at the discretion of their GP or themselves, including physiotherapy, imaging, medications, and specialist consultations. Concomitant care is distinct from the study intervention. All concomitant care for LBP will be recorded at each follow-up time point via patient self-report questionnaires, and complemented where available with health insurance data.

GPs: General practitioners; PTs: physiotherapists; IR: interdisciplinary rehabilitation; ***Patient education resources** are present in the core clinical components (goal: improve patients' beliefs which should influence clinical outcomes – eg. reduce pain & disability) and the implementation strategies (goal: intervening on patients’ beliefs can enhance the uptake and adherence of the intervention amongst GPs).

### Outcomes

2.6

The primary system-level outcome is the incremental cost per quality-adjusted life-year (QALY), estimated using the EQ-5D-5L, incorporating costs from both a healthcare payer and a societal perspective [43]. Direct medical costs over 12 months will be collected through a structured patient-reported healthcare utilization questionnaire administered at each follow-up time point, capturing GP consultations, physiotherapy, specialist visits, investigations (imaging, blood tests), medications, injections, surgery, and hospitalization, previously used in Switzerland [28]. Where available, self-reported data will be complemented and validated using health insurance reimbursement data provided by the main healthcare insurances in Switzerland, covering patients insured by this provider. Indirect costs related to absenteeism and presenteeism will be assessed using the Work Productivity and Activity Impairment Questionnaire (WPAI) [44,45].

The primary practitioner-level outcome is the proportion of patients receiving back-related imaging within 6 months of the initial consultation [29,35]. Secondary practitioner-level outcomes include opioid prescription, medication use, imaging rates and total number over 12 months, clinicians’ beliefs about LBP (measured with the 10-item Back Pain Attitudes Questionnaires, Back-PAQ), and confidence in managing LBP [[46], [47], [48], [49]].

The primary patient-level outcome is back-related disability measured by the 24-item Roland–Morris Disability Questionnaire (RMDQ) at 6 months [50]. Secondary patient-level outcome measures include pain intensity (Numerical Rating Scale, NRS), health-related quality of life (EQ-5D-5L), work participation (WPAI), Global Rating of Change (11-point scale, GRC), pain self-efficacy (Pain Self-Efficacy Questionnaire short form, PSEQ-2), a range of psychological factors, including Fear of movement, Catastrophizing, Anxiety, Depression (Brief screening questions from Kent et al., 2014, BSQ), expectations to return to work (one question from Orebro questionnaire), beliefs about LBP (10-item Back-PAQ) and reassurance (Reassurance Questionnaire) [43,46,[51], [52], [53], [54]]. Based on the advice of our patient partner, two questions were added about capacity to perform valued activities and confidence in their back. PSEQ-2, BSQ and Back-PAQ questionnaires will help investigate the mechanisms of action of the PRIME intervention.

Adverse events (AEs) will be monitored through both passive and active surveillance. Passive surveillance involves continuous self-reporting by participants to the research team or their treating GP. Active surveillance is conducted through REDCap, where participants are prompted to report health events; any declaration triggers an automated alert to the research team for evaluation. Serious AEs are defined as events resulting in death, hospitalization or in persistent disability and are not anticipated given the non-invasive, non-pharmacological nature of the intervention. The expected non-serious AE is a fluctuation or increase in back or leg pain symptoms; this type of event is sometimes referred to as a normal reaction and will not be reported by GPs or physiotherapists.

Healthcare professionals baseline data will include general characteristics such as age, gender, years of clinical experience, practice setting and type, and prior training in LBP management. Patient baseline data will include demographics and social determinants of health. Participants will receive online questionnaire links by SMS and email. To limit participant burden, baseline data will be collected over two timepoints: on the day of the initial GP consultation and two days later. Follow-up assessments will occur at 10 days, 6 weeks, and 3, 6, 9, and 12 months (Supplementary Material S4). To promote retention, non-respondents will receive up to three reminders, followed by telephone contact if needed. Participants may receive financial compensation of up to CHF 50 based on questionnaire completion.

